## 11. STUDY OBJECTIVES

### 11.1 Primary

The primary objective of this study is to determine the safety and tolerability of orally administered moxidectin in subjects with *O. volvulus* infection, as measured by the incidence of clinical AEs and clinically significant laboratory test results.

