## **18. SAFETY**

### **18.1 Safety Variables**

All subjects enrolled in this study will be closely monitored for safety and evaluated for any AEs. Safety evaluation will include: symptoms, physical examinations, vital signs measurement, ECGs, ocular exams, and laboratory evaluations. All evaluations will be monitored as outlined in section 16.1, Procedures, and section 16.3, Special Methods. A key safety component of the study drug will be determined by the presence and severity of the Mazzotti reaction. An important consideration in the administration of microfilaricides to *O. volvulus* infected subjects is the potential for the combination of AEs due to the pharmacologic properties of the drug with the constellation of symptoms, signs and laboratory events that occur when microfilariae are killed (the Mazzotti reaction). These need to be differentiated one from the other and from any coincidental illnesses that may occur in temporal relationship with test drug administration. Common systemic clinical manifestations of the Mazzotti reaction include pruritus, rash, lymphadenitis, headache, myalgia, arthralgia, hypotension, fever and swellings of the face and limbs. Ocular events include epiphora, photophobia, conjunctival injection, limbitis, anterior uveitis, chorioretinitis and optic neuritis.

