For a given intensity of infection, the severity of the Mazzotti reaction to ivermectin is independent of dose within the range of 150 to 800 µg/kg (approximately 9 mg-48 mg). Dangerous and alarming reactions result from the simultaneous occurrence of severe reactions in multiple systems. This phenomenon is rare with ivermectin. Biphasic reactions, characterized by a marked recrudescence of cutaneous or lymph node symptoms or the development of an acute febrile polyarthritides, several days after the initial reaction, have also not been observed with ivermectin. There is no reason to believe that the Mazzotti response to moxidectin would differ radically from those due to ivermectin. However, a more rapid elimination of microfilariae may result in an earlier onset, or a more severe reaction, for a given initial infection intensity.

Severe reactions can usually be aborted by the administration of 100 to 200 mg of hydrocortisone hemisuccinate intravenously aided by supportive therapy.

The clinical events will be graded according to the National Cancer Institute common toxicity table, version 2.0, with additions specific for this protocol summarized in Attachments 5 and 6.

More frequent safety evaluations may be made if clinically indicated or at the discretion of the investigator. All adverse effects (AEs) will be recorded in the CRFs throughout the entire study.

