## **21.2 Methodology**

Initially, an overall among-group test will be performed to determine if any significant differences exist among the 4 treatment groups (2 mg, 4 mg, 8 mg moxidectin, and ivermectin). For this analysis the ivermectin control will be pooled over all nine cohorts (three dose groups). Following a significant overall result, paired comparisons (i.e., each moxidectin group versus ivermectin) will be performed to characterize the results. Prior to pooling the nine cohorts the ivermectin response for the nine cohorts will be graphically evaluated to ensure that there is no time effect on the pooled ivermectin results. For safety, moxidectin will be compared with ivermectin with respect to the incidence of AEs by using the Fisher's exact test. Laboratory data will be analyzed by using the analysis of covariance, adjusting for baseline. For efficacy, the microfilariae counts will be logarithmically transformed (Mosteller and Tukey) and analyzed by using the analysis of covariance, adjusting for baseline counts and the number of sites from which the microfilariae were taken. The latter covariate will be used to adjust for subjects who have fewer than 4 microfilarial collection sites. Factors in the model will include treatment group, covariates, level of microfilariae density (mild, moderate, severe), and gender. Also, a sensitivity analysis will be performed to examine the effect on results of second-order interactions. Data results will be summarized as adjusted geometric means. If the assumptions of normality or log-normality are not met, the data will be analyzed by using the Friedman Test, blocking on baseline skin microfilariae density and gender. In order to evaluate the robustness of the results, the microfilariae data will also be analyzed as a percent change from baseline. The proportion of subjects cured (i.e. with undetectable microfilariae) will also be evaluated.

For the analysis of microfilariae viability and fertility endpoints, proportions will be analyzed by using the Cochran-Mantel-Haenszel procedure blocking on baseline skin microfilariae density. If the overall test is significant, paired comparisons will be made comparing each moxidectin group with ivermectin.

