SAEs that are not test article related may nevertheless be considered by the participating investigator or the medical monitor (or designee) to be related to the conduct of the clinical study, ie, to a subject's participation in the study. For example, a protocol-related SAE may be an event that occurs during a washout period or that is related to a procedure required by the protocol.

The severity of AEs will be assessed according to the Onchocerciasis Chemotherapy Research Centre Common Toxicity Criteria (OCRC CTC), version 2.0, 1980, 1992, 1999 2006 and according to the National Cancer Institute Common Toxicity Criteria (NCI CTC), version 2.0, April 30, 1999 for all those AEs not included in the OCRC CTC ~~a. Additions to this grading scale for OCRC CTC can be found in ATTACHMENT 5 ocular, hematological and biochemical adverse events can be found in Attachments 5 and 6 respectively.~~

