| Toxicity                                                                                                                                                                    | 0      | 1                                        | 2                                                           | 3                                                                                                           | 4                                                                                                                       |
| MAZZOTTI TOXICITY CRITERIA (MTC) SYSTEMIC (1)                                                                                                                        |        |                                          |                                                             |                                                                                                             |                                                                                                                         |
| Itching                                                                                                                                                                     | None   | Mild                                     | Moderate or 'Severe' but with only occasional scratching    | 'Severe' and with fairly vigorous scratching "Windmill Effect"                                              | 'Severe' and with restlessness, agitation, loss of epithelium or prolonged vigorous scratching                          |
| Note: 'Severe' is patient's perception of grade of discomfort. "Windmill Effect" = arms in fairly continuous motion with scratching                                         |        |                                          |                                                             |                                                                                                             |                                                                                                                         |

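### Section 21.2 compares clinical AEs between arms only on incidence, with no grade threshold, although the protocol treats Mazzotti severity as a key safety component and already grades it

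*Supplement*

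**What the plan says.** All references are to the latest protocol version in the supplement; no separate SAP is shown.

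- Section 11.1 makes safety and tolerability the primary objective, "as measured by the incidence of clinical AEs and clinically significant laboratory test results".
- Section 18.1: "A key safety component of the study drug will be determined by the presence and severity of the Mazzotti reaction". It adds that, although no radical difference from ivermectin is expected, "a more rapid elimination of microfilariae may result in an earlier onset, or a more severe reaction, for a given initial infection intensity".
- Section 23.4: "The severity of AEs will be assessed according to the Onchocerciasis Chemotherapy Research Centre Common Toxicity Criteria", with the NCI criteria for events not covered there. In Attachment 5 itching runs from mild (grade 1) to grade 4, described as "Severe' and with restlessness, agitation, loss of epithelium or prolonged vigorous scratching". Most items run 0 to 4; rash stops at 3.
- Section 21.2: for safety, "moxidectin will be compared with ivermectin with respect to the incidence of AEs by using the" Fisher's exact test. Laboratory values get an analysis of covariance. No other test of clinical AEs is named.
- Grade appears in two other places. Section 21.3 gives the chance of seeing at least one AE of grade 2 or higher in a moxidectin group. Section 18.2 asks the expert reviewers to look at counts of drug-related AEs before each dose step. Neither is a statistical comparison between arms.

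**The concern.** Both drugs kill microfilariae, so both can provoke Mazzotti reactions. The difference that Section 18.1 foresees is in how bad the reaction is, or how early it comes, more than in whether it occurs. A yes/no test on any grade counts mild itching and agitated itching with skin loss as the same event.

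Two things follow. If only severity differs between arms, the null hypothesis of the planned test is true and the test has nothing to find. If reactions worsen at every grade, the test uses only the boundary between none and any, and loses information, most of all when nearly everyone reacts. Because safety is the primary objective, a non-significant incidence test could be read as similar tolerability when the grades differ.

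**Working it through.** **The plan's own AE figures.** With P = 1 − (1 − p)^n, n = 12 gives 0.1136 (p = 1%) and 0.7176 (10%); n = 24 gives 0.2143 and 0.9202. All four figures in Section 21.3 reproduce. They describe a single arm and say nothing about the power of a comparison.

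**Inputs.** From the documents: 48 subjects per moxidectin dose and 48 pooled ivermectin subjects (Section 21.3); two-sided 0.05 (Section 21.2); grades 0 to 4 (Attachment 5). Not in the documents, so assumed: incidence and grade spread on ivermectin, and the size of the shift. All tests below are unstratified, so that only the scale differs.

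**Case A: every grade cut-off shifts by a common odds ratio of 2.5.** Incidence moves from p to 2.5p / (1 − p + 2.5p); for example 50% becomes 1.25/1.75 = 71.4%, and 85% becomes 2.125/2.275 = 93.4%. Assumed ivermectin probabilities for grades 0 to 4 are (.50, .25, .15, .08, .02), (.30, .30, .25, .12, .03), (.15, .35, .30, .16, .04) and (.05, .35, .35, .20, .05) for 50, 70, 85 and 95% incidence. In the grade ≥2 row, the 20% and 40% columns spread reactors over the grades as in the 50% column. That puts grade ≥2 on ivermectin at 10, 20, 25, 40, 50 and 60%. The any-grade and rank rows are simulated; the grade ≥2 row is exact.

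| Any-grade incidence, ivermectin | 20% | 40% | 50% | 70% | 85% | 95% |
|---|---|---|---|---|---|---|
| Fisher, any grade | 44% | 53% | 49% | 34% | 15% | 1% |
| Fisher, grade ≥2 | 25% | 43% | 47% | 53% | 49% | 44% |
| Wilcoxon on worst grade | 54% | 66% | 69% | 69% | 70% | 68% |
| Wilcoxon minus any-grade Fisher | 10 | 13 | 20 | 35 | 55 | 67 |
| Wilcoxon minus grade ≥2 Fisher | 29 | 23 | 22 | 16 | 21 | 24 |

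With no true difference the Wilcoxon test rejects in 4 to 6% of simulations, so its gain is not inflated type I error.

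**Case B: incidence equal, severity worse.** Reactors are spread over grades 1 to 4 as 60/30/8/2% on ivermectin and 30/40/22/8% on moxidectin.

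| Incidence, both arms | 40% | 60% | 80% | 90% | 95% |
|---|---|---|---|---|---|
| Fisher, any grade | 3% | 3% | 3% | 2% | 1% |
| Fisher, grade ≥2 | 22% | 38% | 59% | 70% | 75% |
| Fisher, grade ≥3 | 15% | 31% | 46% | 54% | 58% |
| Wilcoxon on worst grade | 8% | 21% | 51% | 75% | 84% |

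Pooling the three doses (144 vs 48) leaves any-grade Fisher at 3.8% at 90% incidence; hence at most about 4%. With a milder shift (odds ratio 2.5 among reactors) at 50% incidence, Fisher on grade ≥2 has 14% and the rank test 9%. The rank test is therefore not the best tool for a pure severity shift when incidence is low or moderate.

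**The case against.** **Incidence is not said to mean any grade.** This stands. Section 21.2 sets no threshold, and Sections 21.3 and 18.2 both work with grade 2 or higher for at least part of their content. Fisher's test at grade 2 or higher would contradict nothing. But the text does not choose that reading, and under it the rank test still gains 16 to 29 points in Case A.

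**The size rests on assumptions.** This also stands. A reader might infer that a more severe reaction to moxidectin will mostly be missed. The documents do not support that in general. At 40 to 60% incidence and an odds ratio of 3, any-grade Fisher still has 58 to 69% power, and single Mazzotti items may be less common than that. The documents' figures that suggest a ceiling are 62.1% treatment-emergent AEs over 180 days in healthy volunteers (Section 9) and fluorescein reactions in 18 to 38% (Section 14.2). If independent, they combine to 1 − 0.379 × 0.82 = 69% up to 1 − 0.379 × 0.62 = 77%. That is any AE of any kind, not a Mazzotti item.

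**Severity is not ignored.** Reviewers who may unblind look at non-CNS AEs of grade 2 or higher before each dose step, and that item does not set Mazzotti reactions aside (the CNS and SAE items do). A marked excess could be seen there or in descriptive tables. This is judgement for dose progression, not an estimate of the treatment difference.

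**Detail may be left to a SAP.** Tables of AEs by grade may well be. The point here is not missing detail: the protocol states a test, and that test uses less of the recorded data than its own safety question needs.

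**Conclusion.** The point holds in limited form. The only between-arm test of clinical AEs is on incidence without a threshold, while the protocol names severity as part of its key safety question and collects it. Two statements rest on the test itself: an any-grade incidence test cannot detect a pure severity shift (power at most about 4%), and it uses only one of the grade boundaries. The size of the loss under a general shift is conditional on the assumed odds ratio of 2.5 and the assumed incidence: about 10 to 20 points at 20 to 50%, about 35 at 70%, and more than 50 from 85% upward. A common odds ratio is also the pattern that suits a rank test best. The claim that severe reactions would mostly go undetected is justified only near the ceiling or when incidence does not differ. The sponsor should amend the analysis, but nothing here shows that a safety signal would be lost to the reviewers.

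**What to change.** In Section 21.2:

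1. Add a prespecified comparison of each subject's worst post-dose Mazzotti grade, overall, for each moxidectin dose against ivermectin, by a van Elteren test or a proportional-odds model within the existing microfilarial density strata.
2. Add Fisher's exact tests on incidence of grade 2 or higher and of grade 3 or higher, since these do better than the rank test when only severity shifts and incidence is low to moderate.
3. Give the same comparison per item as supportive. Attachment 5 lists 11 items under its two Mazzotti systemic headings, so three doses give 11 × 3 = 33 tests; label them exploratory or adjust for multiplicity.
4. Keep any-grade incidence as a supporting summary, and state that it is any grade.

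The cost is wording in the statistical section, more tests and tables, and an effect measure less familiar than a difference in incidence. Grades are already recorded under Section 23.4, so no new data, visits or subjects are needed.

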The clinical laboratory changes involve the peripheral blood leucocytes, aspartate aminotransferase (AST/SGOT) and alanine aminotransferase (ALT/SGPT) and sometimes lactate dehydrogenase (LDH) and gamma-glutamyl-transferase (GGT); microfilariae also appear in blood, urine, and other body fluids. The eosinophils exhibit the most prominent changes. There may be an initial eosinopenia followed several days later by a marked increase above pretreatment levels. A complete disappearance of eosinophils from the peripheral blood is the laboratory hallmark of a severe reaction. Lymphocyte counts may fall initially, followed by lymphocytosis, but not to the same extent as with eosinophils. Leucocytosis with neutrophilia is less common. Elevations in liver enzymes occur, but rarely exceed grade 2 and usually normalize by day 30. Levels of bilirubin and alkaline phosphatase are usually unchanged. Any deviation from this pattern of liver function abnormalities should prompt investigations for an intrinsic drug effect or a coincidental illness. Proteinuria may occur. Although the laboratory changes per se have little clinical significance, they give indirect evidence of the death of microfilariae and may even indicate the speed and severity of the reaction to the event.

The factors that govern the Mazzotti reaction include the intensity of infection, the dose regimen, and the microfilaricide used. These determine the onset, evolution, reaction severity, extent of the laboratory changes, and whether the reaction is mono- or biphasic. A notable exception occurs in subjects with hyper-reactive onchodermatitis (Sowda), where severe, predominantly cutaneous adverse effects occur even with very low skin microfilarial counts.

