### **18.3 Safety Laboratory Determinations**

All clinical and laboratory evaluations that deviate from baseline values after study drug administration and are considered to be clinically significant will be repeated and followed until normalization. If normalization does not occur within 2 weeks or by day 30, the etiology will be identified, if possible, and the Wyeth medical monitor, the WHO clinical monitor, and the WHO project manager, will be notified.

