## **21. STATISTICAL ANALYSIS**

### **21.1 Statistical Methods**

This is a randomized, double-blind, active-control, dose-escalation trial comparing 3 doses of moxidectin (2, 4, and 8 mg) with ivermectin, stratified by microfilariae density (mild, moderate, severe) and gender. Subjects will be treated as in subjects for the first 18 days and as outpatients for the remainder of the 18 month study.

The primary analysis population for safety will be the modified intent-to-treat (mITT) population, which consists of all subjects who receive study medication. For efficacy, the primary analysis population will be the evaluable subject population, which is defined as all subjects who receive study medication and have baseline and 18-month microfilariae count data. An mITT sensitivity analysis will also be performed to evaluate the effect on the efficacy results of dropouts occurring before 18 months.

The primary objective of the study is to evaluate the safety of escalating moxidectin regimens. Both the incidence of clinical AEs and clinically significant laboratory test results will be used to assess safety.

The primary efficacy endpoint is the reduction from baseline in skin microfilariae at 18 months. Microfilariae count will be defined as the geometric mean of skin microfilariae/mg taken at 4 sites (iliac crests and calves).

In addition, important secondary endpoints are the reduction from baseline in skin microfilariae load at day 8, 1 month, 2 months, 3 months, 6 months and 12 months, area under the curve (calculated by using the trapezoidal method through the 18 month visit), ocular examination (time of maximum reduction of microfilariae and number (%) of subjects with complete clearance) and nodulectomy (viability and fertility of macrofilariae) at 18 months.

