## **23. ADVERSE EVENTS**

### **23.1 Definitions**

The term "adverse event," as used by the sponsors, is synonymous with the term "adverse experience," which is used by the FDA.

An ***adverse event*** is any untoward, undesired, unplanned clinical event in the form of signs, symptoms, disease, or laboratory or physiological observations occurring in a human being participating in a clinical study with a sponsor's test article, regardless of causal relationship. This includes the following:

- Any clinically significant worsening of a preexisting condition.
- An AE occurring from overdose of a sponsor test article whether accidental or intentional (ie, a dose higher than that prescribed by a health care professional for clinical reasons).
- An AE occurring from abuse of a sponsor's test article (ie, use for nonclinical reasons).
- An AE that has been associated with the discontinuation of the use of a sponsor's test article.

Note: A procedure is not an AE, but the reason for a procedure may be an AE.

A ***preexisting condition*** is a clinical condition (including a condition being treated and AEs occurring between ICF signing to the subject's arrival at the clinic) that is diagnosed or occurs before the screening of the subject for this study is initiated in the hospital. A preexisting condition can be part of the subject's medical history or part of baseline conditions and are recorded in the source records and on the appropriate page of the CRF (for randomized subjects).

Baseline conditions are all those clinical conditions, including those related to infection with *Onchocerca volvulus*, present at the time of screening. Medical history are all clinical conditions known to have been present prior to screening. A condition can be both part of the medical history and baseline conditions if the condition started prior to screening and is still present at screening (e.g. any condition related to infection with *Onchocerca volvulus*).

Adverse events occurring during and due to screening procedures will be recorded as adverse events.

AE collection on source documents starts on the date of subject's arrival at the clinic / start of screening. From this time point, any SAEs are reported to Wyeth within 1 business day from their occurrence.

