  2. Test article abuse and overdose (ie, use for nonclinical reasons) with or without AEs. An overdose is a dose higher than that prescribed by a health care professional for clinical reasons. It is up to the participating investigator to decide whether a dose was an overdose.
  3. Inadvertent or accidental exposure to test article with or without an AE.
    - Poststudy test article-related SAEs.
    - SAEs occurring after unauthorized or accidental use in persons not participating in the study.
    - Abnormal biological or vital signs values that are considered clinically relevant by the participating investigator. These must be reported in the same time frame and following the same process as for an AE or an SAE.

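### The primary safety objective counts subjects with clinically significant laboratory results, but the only laboratory analysis named in section 21.2 compares mean values

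*Supplement*

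**What the plan says.** References are to the amended protocol; no separate analysis plan is shown.

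- Section 11.1 sets the primary objective as safety and tolerability, "as measured by the incidence of clinical AEs and clinically significant laboratory test results". Section 21.1 repeats it: "Both the incidence of clinical AEs and clinically significant laboratory test results will be used to assess safety".
- Section 21.2 gives one method to each part. For adverse events, "moxidectin will be compared with ivermectin with respect to the incidence of AEs by using the Fisher's exact test". For laboratory values, "Laboratory data will be analyzed by using the analysis of covariance, adjusting for baseline". It states no visit, scale or transformation for the laboratory ANCOVA. The log transform in that section is specified for microfilariae counts.
- Section 18.3 says that laboratory deviations "considered to be clinically significant will be repeated and followed until normalization", but attaches no grade or cut-off to the term.
- Section 23.1 defines an adverse event as an untoward event "in the form of signs, symptoms, disease, or laboratory or physiological observations". Section 23.3 has the following reported like an AE or SAE: "Abnormal biological or vital signs values that are considered clinically relevant by the participating investigator". Section 23.4 grades AEs by the OCRC CTC.
- Attachment 5 (OCRC CTC) grades laboratory values. Eosinophils are graded in both directions: grade 2 is 14-19/mm³ on the low side and above 2850 up to 5700/mm³ on the high side.
- Section 18.1 describes the expected course: "There may be an initial eosinopenia followed several days later by a marked increase above pretreatment levels". It treats complete loss of eosinophils as the laboratory mark of a severe reaction.

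**The concern.** The objective asks in how many subjects a laboratory result became clinically significant. The named method asks whether mean values differ. These can part company in both directions. Means can differ when no value is abnormal, and they can agree when abnormal values are more frequent in one arm, especially for analytes graded low and high.

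At stake is one of the two stated components of the primary safety measure. Followed as written, section 21.2 yields a set of mean differences and no estimate of the quantity that sections 11.1 and 21.1 name. A dose could be described as free of laboratory signals without anyone having compared the proportions affected.

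**Working it through.** **1. The plan's own safety figures.** Section 21.3 sizes safety on the chance of at least one AE of grade 2 or higher, 1 − (1 − p)^n:

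- n = 12: 1 − 0.99^12 = 0.114; 1 − 0.90^12 = 0.718
- n = 24: 1 − 0.99^24 = 0.214; 1 − 0.90^24 = 0.920

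All four reproduce. Safety is therefore sized on counts of graded events, not on means.

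**2. Mean shift with nothing abnormal.** Group sizes are 48 and 48 and alpha is two-sided 0.05 (sections 21.2 and 21.3). The baseline correlation of 0.6 is assumed. The residual SD is √(1 − 0.36) = 0.8 SD, and the standard error is 0.8 × √(2/48) = 0.163 SD.

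- Shift 0.5 SD: 0.5/0.163 = 3.06; power ≈ Φ(3.06 − 1.96) = 86%
- Shift 0.3 SD: 0.3/0.163 = 1.84; power ≈ Φ(1.84 − 1.96) = 45% (43% by simulation)

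This is ordinary ANCOVA power. It applies whether or not any value is out of range.

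**3. Eosinophils.** The documents give no laboratory SD or event rate, so everything here is assumed. Normal values are lognormal with median 600/mm³ and log-SD 0.5, kept within the ungraded range 27-1425, with baseline correlation 0.6. Low results are uniform on 0-13/mm³ and high results uniform on 2850-5700/mm³. Each comparison has 48 v 48 subjects and 1500 to 3000 simulated trials. The incidence test is Fisher's exact test on the proportion flagged; its power is the exact sum of binomial probabilities over all rejecting tables.

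| Ivermectin (low/high) | Moxidectin (low/high) | ANCOVA raw | ANCOVA log | Fisher, exact |
|---|---|---|---|---|
| 5% / 5% | 25% / 10% | 5-6% | 59-61% | 80% |
| 5% / 5% | 20% / 15% | 18-19% | 26-27% | 80% |
| 5% / 5% | 30% / 5% | 15-19% | 87-88% | 80% |
| 5% / none | 25% / none | 48-49% | 78-80% | 72% |

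Repeat simulations put Fisher within about two points of these exact values (up to 82% and 74%). The first three rows share one true difference in incidence, 10% v 35%. The incidence test has the same power in each; ANCOVA runs from about 5% to 88% according to how the excess splits and which scale is used.

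Hand check of row 1, raw scale, taking a normal value as 600 and the midpoints 6.5 and 4275:

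- extra lows: −0.20 × (600 − 6.5) = −119
- extra highs: +0.05 × (4275 − 600) = +184
- net difference: +65/mm³
- variance from the highs alone: 3675² × (0.05 × 0.95 + 0.10 × 0.90)/48 = 38,688, so SE ≈ 197
- 65/197 = 0.33 SE, giving power of about 6%

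**4. Fall and rise at separate visits.** This is the course that section 18.1 describes. With 20% low and 20% high against 5% and 5%, medians 300 to 1000/mm³ and log-SD 0.6 (600 runs), ANCOVA by visit gives:

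- at the fall: raw 24-38%, log 54-61%
- at the rise: raw 58-60%, log 44-50%
- Fisher on either abnormality: 83-86%

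**5. One-directional analytes.** For ALT at 2% v 20% above 2.5 × ULN, ANCOVA and Fisher both have 75%.

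**6. Power of the incidence test itself,** 48 v 48: 5% v 20%, 48%; 5% v 30%, 88%; 10% v 20%, 18%; 10% v 30%, 61%.

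**The case against.** Four objections carry weight.

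**Laboratory events can reach an incidence test.** The AE definition covers laboratory observations, clinically relevant values are reported like AEs, Attachment 5 grades them, and AE incidence goes to Fisher's test. A reader might infer that laboratory abnormalities are tested only through means; the documents do not support that. But the route depends on the investigator's judgment, with no grade that triggers it. Section 18.1 describes the Mazzotti laboratory changes as having little clinical significance in themselves, so many may never be recorded. Section 21.1 also lists laboratory results apart from clinical AEs.

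**Cut-offs and tables usually belong in an analysis plan, and none is shown.** That excuses a missing table layout or threshold. It does not excuse section 21.2 from naming a specific method that targets a different quantity.

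**Cancellation is not the expected pattern.** Section 18.1 puts the fall and the rise days apart, and laboratory samples fall on separate days. A reader might infer that eosinophil toxicity would be largely missed. That is not shown: at the visit of the fall, log-scale ANCOVA does as well as or better than Fisher (80% v 74% as simulated, for 25% v 5% low). The weakness belongs to the raw scale and to mixed directions at one visit. All rates are assumed.

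**Graded is not the same as clinically significant.** This is fair, and it argues for a definition fixed in advance. Nor does section 21.2 equate a significant ANCOVA with a clinically significant result, so a reader should not infer that harmless shifts would be reported as safety signals.

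**Conclusion.** The mismatch between objective and method stands on the text alone. Sections 11.1 and 21.1 name an incidence; section 21.2 supplies a comparison of means and no laboratory-specific incidence analysis; clinically significant has no definition. Capture through AE reporting is partial and discretionary.

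The cost in sensitivity is conditional. Under the assumed rates, raw-scale ANCOVA falls well below an incidence test for two-way or low-side eosinophil abnormalities (about 6-49% against 72-80%, or 74-82% in some simulation runs). It loses little or nothing on the log scale at the visit of the fall, or for one-directional analytes such as ALT. On the raw scale it also comes close when high values dominate: 80-91% against 84-93% for 10% low and 30% high v 5% and 5%. The plan fixes neither scale nor visit, so nothing secures the favourable case. Even a significant ANCOVA would leave the stated question unanswered, because it gives no count of affected subjects.

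This should be corrected. It does not threaten the validity of the trial.

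**What to change.** In section 21.2, or in an analysis plan written before unblinding:

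1. Make the main laboratory safety analysis the per-subject incidence of clinically significant post-dose results.
2. Define such a result in advance as a stated worsening from baseline on the existing OCRC CTC grades. Count low and high separately and together, and keep expected Mazzotti changes identifiable. The clinical team should choose the grade.
3. Compare each moxidectin dose with pooled ivermectin by Fisher's exact test, with the difference in proportions and its confidence interval.
4. Keep ANCOVA of values as supportive, with the visit and scale stated for each analyte.
5. State when a graded laboratory value is to be recorded as an AE, so that the overlap between the two analyses is known.

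The laboratory values and the grading scale are already in place. The cost is wording and one set of tables. The limitation is low power for modest differences (about 18% for 10% v 20%), so the confidence intervals should carry the interpretation and a non-significant result should not be read as absence of harm.
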